**Other secondary outcomes**

Other secondary outcomes will include service use, processes and implementation outcomes including, for example, number of antenatal checks, number of antenatal checks with blood pressure measurement, number of referrals, postnatal check within a week of birth.

Fidelity: number of mentors and team coordinators recruited; number of training packages and workshops provided for mentors and teachers: number of weekly 1:1 meetings between mentors and mentee; number of monthly social gatherings and attendees; proportion of women being accompanied by mentees to register for antenatal care, during labour and to purchase first supply of goods; number of visits from mentor to mentee’s family.

Acceptability: satisfaction with differet components of the intervention among young girls, mentors, healthcare providers and local stakrholders

Reach: number, proportion of participating young women when compared to the site population included

Adoption: engagement and updake of the mentoring scheme: proportion of site areas providing the mentoring scheme; number of sites interested in implementing the mentoring program.

Women’s experiences of mentoring and care (e.g., respectful care, access, trust, system responsiveness, quality and safety, attitude to and uptake of contraception in the postnatal year) *and* economic and social progress/wellbeing (e.g measures, return to education, set up a business, perspectives of thriving)

Mechanisms of change for health outcomes (e.g. access to care, advocacy, support, respectful care, engagement, referral and escalation, health promotion and empowerement, relationships) and for social and economical wellbeing (e.g. social and economic empowerment, self-confidence, sense of agency, trustworthy adult and peers, respectful community engagement with families)

# Clusters description

Each cluster will be described according to the number of primary, secondary and tertiary facilities and their referral distances. Details on staffing levels and availability of key resources (e.g. neonatal care, blood transfusion, magnesium sulphate) will be collated. In addition, major changes to the trial catchment, such as changes to infrastructure, policy, patient payment requirements or environmental conditions (e.g. physical and cultural context around teenage pregnancy, management of complications, escalation of care, referrals systems) will be reviewed systematically.

# Data collection

Primary and secondary pregnancy outcome data collection

Outcome data will be recorded over the study period and will be collected at an individual level. Recent stakeholder engagement has identified the routine data collection tools used to collect routine data (ANC attendance register, birth register, referral register, 6-week postnatal check appointment book). At some PHUs, an additional ‘adolescent book’ is in use to record ANC registration of under-18-year-olds and associated birth outcomes). Regular visits to PHUs by data collectors will use these to identify under-18-year- presenting at the health facility (e.g. registering for ANC, delivering their babies in the PHU or in a referral hospital, or attending the PHU for the 6-week postnatal appointment) and will allocate each a unique study number which will be recorded in a book that is kept securely in the clinic in the same way as the clinic health registers. Routine practice is for women who do not return for infant immunisations at 6 weeks post-natal to be followed up in the community by a community health worker (CHW). This will allow for maternal deaths in the 42 days after birth, and for neonatal deaths up to 28 days to be included as part of the routine data collection. At the 6 weeks routine postnatal appointment, young mothers in both arms will also be given the option to individually enrol and participate in the sub-studies (e.g. qualitative interviews, photovoice), in order for qualitative data to be collected at around one year (e.g. experiences of care, acceptability, use of contraception, plans to return to education or training, business set up). As mentioned in the application, for those agreeing to participate in the sub-studies, explicit consent will be gained.). Adolescent girls identified by the research assistant who have a disability and/or recently completed the mentoring programme at pre-trial sites may also be invited to take part in the photovoice project. One year infant routine data will be collected from the infant immunisations registry.

The following table represents various scenarios and strategies for data collection in these scenarios:

| Scenario | Strategies to mitigate lost data |
| --- | --- |
| Girl attends ANC, gives birth at PHU and attends 6-week check at PHU | N/A |
| Girl attends ANC but does not give birth in the PHU (maternal death, stillbirth or neonatal death may be missed) | Most likely girl has moved to another area    Liaise with referral hospital to cross-check birth register. If not there;  Data collector to visit address in AN register. If not found;  Connection with midwife investigators from MDSR teams in intervention sites to detect any maternal deaths in community. |
| Girl does not attend ANC but comes to PHU in labour | N/A. |
| Girl attends ANC at PHU but is referred for antenatal complication (very young, very small, sickle cell, twins, breech etc) (maternal death, stillbirth or neonatal death in referral hospital may be missed) | Since she will not necessarily arrive by ambulance, she will be harder to track than emergency transfer in labour.  However, we will liaise with da or HCW at referral hospital to cross-check birth register. |
| Girl attends ANC at PHU but is transferred in labour as an emergency (maternal death, stillbirth or neonatal death in referral hospital may be missed) | Through regular liaison with the referral co-ordinator in nearest referral hospital will find outcome data on girls who are referred. |
| Girl gives birth at PHU but does not attend for 6-week PN appointment (neonatal death, postpartum maternal death might be missed) | CHWs are routinely sent out to check on women who default at 6 weeks. |

Data collection at intervention and control sites will be done by data collectors. Data collectors will be responsible for entering the data anonymised onto MedSciNet, the study-specific management system. To prevent double counting, the research assistant will use their regular visits to ensure no patient is counted twice according to patient identifiers (e.g., in the community and at facility or for maternal and neonatal death).

We are confident, (through interaction with local community workforce and current local initiatives to ensure maternal death reviews), that it is unlikely that most primary outcome events will be missed. We will apply a flexible approach to individualise our methodology according to local capacity and CHW workforce infrastructure.

Consistency and quality of source data will be monitored by the research assistant and CIs. MedSciNet allows for extensive monitoring and query processing features, as well as a comprehensive alerting system to identify missing data. Fields including ‘limits’ will be used to avoid entry of erroneous data. The research assistant will monitor data entry by each data collector continuously on MedSciNet. They will be able to filter and identify any problem areas and validate 10% of the source data to check for transcription errors. It will be possible to review the audit trail at individual levels.

Process Evaluation: experiences and implementation

In line with the current best practice in implementation research, the team will undertake a process evaluation to understand variations in the impact of the intervention on outcomes of interest and to contextualise findings. This will be guided by the Medical Research Council (MRC) guidance for the evaluation of complex interventions and will use mixed methods to assess implementation outcomes and identification of mechanisms and contextual factors that may influence variation in outcomes and experiences across multiple stakeholder groups, and at different stages of implementation. This offers a 360-degree evaluation, which considers needs and perspectives that typically differ between stakeholder groups and can vary over time.

Both quantitative and qualitative data on processes and implementation will be collected from monthly checklists, separate focus groups with a purposive sample of mentors, PHU healthcare staff and other community stakeholders such as teachers and community elders (n≈4), and semi-structured interviews with young women in control and intervention sites (n≈40). If appropiate, a family member or a friend will also be invited to participate in an interview. Women will be offered the opportunity to be one-to-one (interviewer and participant) or one-to-two (interviewer and participant with chosen family members/friend). Thus, if appropriate, family member/friend can be invited to the interviews as social support is culturally patterned and could play an important part in the mechanisms of the intervention, particularly in women’s engagement with care. Interview administered wellbeing measures will include, for example, PHQ-9, the flourishing scale for adolescents, women’s empowerment scale. A small sub-group of participants (n≈6-10) will also be invited to take part in the photovoice pilot project^18^.

Considering how different contexts may affect implementation, as well as the intervention itself, will allow a flexible approach to future scaling up based on this understanding. The following table indicates possible research questions which will be refined in forthcoming stakeholder workshops and will be discussed in focus groups discussions and interviews:

| Context item | Possible interaction with implementation | Specific examples |
| --- | --- | --- |
| Geographical | Rural vs urban settings?  Seasonality – how do the seasons impact on the implementation of 2YL. | In rural settings, how are mentees supported with small business option when there is no local market?  Do monthly gatherings still take place in the rainy season?  Can mentoring mitigate the 2^nd^ delay when roads are impassable in the rainy season? |
| Socio-cultural | Family make-up: living with birth parents / relatives; married (child marriage) vs unmarried  Tribal, religious, ethnic norms and beliefs | Where child marriage is common, how does being married impact on the empowerment 2YL confers?  Is there a reluctance from husbands for married girls to enrol in 2YL? How can this be overcome?  Are there characteristics of tribal, ethnic and religious groups that impact on the acceptability of 2YL? (Various elements such as business, education, contraception) |
| Socio-economic | Economic status of family, especially if girl’s mother is single, or she is living with relatives.  Economic status of area. Some villages have higher levels of poverty.  Seasonal poverty, especially with climate change effects on rainfall. | What are the factors which make some girls’ businesses succeed and others fail? Can 2YL be adapted to mitigate this?  Do girls from poorer backgrounds benefit more from the small business?  Are there any risks associated with being given money for the small business?  How do seasonal effects impact? |
| Ethical | The level of stigma in community. Does this reduce over time?  Disrespectful care | How does 2YL affect the stigma associated with teenage pregnancy? Anecdotal examples of chief publicly speaking out against child marriage, and promoting return to education.  What are the key elements of the community engagement which lead to stakeholder buy-in?  How does 2YL impact at meso level as well as micro level? How do ‘new’ sites and ‘old’ sites differ in the impact 2YL has on  Does 2YL mitigate disrespectful care? |
| Political / legal | Government policies around teenage pregnancy and child marriage; high levels of law enforcement; new strategy | How do government policies ‘hands off our girls’ and ‘radical inclusion’ (in education) interact with 2YL and the willingness of communities to engage?  Is the law counter-productive in that it keeps girls away from ‘authority figures’ (health staff), for fear of being targeted / blamed / having their partner or parents arrested? |

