# Background and rationale for study

Maternal mortality in Sierra Leone is one of the highest globally (1,360 deaths per 100,000 live births in 2015)^1^ with teenage pregnancy a leading cause of death for mothers; teenage mothers are 40-60% more likely to die during childbirth.^2^ However due to ineffective maternal death reporting, this could be significantly higher. A household survey conducted in 2015 indicated a maternal death rate of 1 in 10 for under-18-year-olds in Eastern Freetown. A following study examined the causes of this high incidence of maternal death in teenagers and highlighted intersecting health and socio-economic vulnerabilities.^3^ Among key findings were that pregnant teenagers are often neglected by their families, particularly when being cared for by a non-parental adult, often sleeping on bare ground without a mosquito net, and are fed once a day in exchange for heavy domestic duties such as water collection and laundering, in many cases with little protection from ongoing gender-based violence. This lack of adult care or support often leads to delays in care-seeking or complete lack of antenatal and delivery care, putting teenagers at high risk of death from undetected pre-eclampsia, untreated infections, anaemia, lack of birth preparation, and common obstetric risks.^3^ To achieve the Sustainable Development Goals target of reducing the maternal mortality rate to less than 70 per 100 000 live births by 2030, adolescent girls are a priority group. ^4-6^

These findings led to the development of 2 Young Lives (2YL), a locally-designed intervention that provides mentoring from pregnancy through to one-year post-birth for women aged under-18. This encourages mentees to take up antenatal care and hospital birth, re-establish family connections where this is safe and appropriate, promotes health-seeking behaviour, provides practical advice about childbirth, parenting and contraception, and supports mentees to return to education or start vocational training. The 2YL scheme was piloted in 2017/2018 in an urban suburb of the capital, Freetown, and expanded to new sites in 2018, 2019 and 2021.^7^

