# How the 2YL intervention may work

Overall, the aim of 2YL is that mentees and their babies survive birth and the postnatal period, and that these young women are empowered economically and socially to thrive. A theory of change diagram in Figure 1 in page 8 illustrates how and why the 2YL intervention may work in young women in Sierra Leone.

After community engagement with key community stakeholders, volunteer mentors are recruited and trained to support mentees across a number of domains. The 4-day manualised training programme uses discussion, role play and bespoke pictorial maternal health resources to learn and share important health messages. Key ingredients of the mentoring scheme include a weekly one to one meeting, promotion of health services uptake, monthly social gatherings for peer support and health discussions, advocacy and practical advice, support to start and run small businesses, and encouragement to return to education or start vocational training.

There are a number of mechanisms whereby being mentored could lead to improved health outcomes for mothers and their babies:

- Mentors ensure that girls access antenatal care, often paying for routine drugs when not available in the clinics, and directly observing the girls taking them. They ensure birth with a Skilled Birth Attendant, a proven life-saving intervention. In addition, the timeliness and quality of this care, and the quality of interaction with the girl in the health facility may be improved by the her being accompanied by a known and respected older woman in the community^9^; mentors are often allowed to be present for birth. Getting to know a health worker through monthly facilitated discussions and regular antenatal care could also increase girls’ confidence in the health service, increasing their likelihood of seeking care in labour or in an emergency. Similarly, having a trustworthy adult in their lives also allows mentees to ask advice of mentors and access care promptly.
- Girls are economically empowered through their small businesses, which could lead to a better diet in pregnancy, potentially addressing risk factors for maternal mortality such as malnutrition and anaemia. This economic empowerment could also allow girls to make independent decisions when to go to hospital as they could pay for their own transport^10^.

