Suboptimal maternal health care contributes to premature deaths, disability, and devastating spending in a country with an incipient financial crisis exacerbated by the 2014 Ebola epidemic (and further weakened during the ongoing COVID-19 epidemic). It has the highest maternal mortality rates in the world (1,360/100,000) with teens accounting for nearly 40% of all maternal deaths (more than two thirds caused by pre- eclampsia, haemorrhage and sepsis). Neonatal, infant and child mortality are also high (31.8, 83.5 and 11/1,000 respectively) and infants of mothers who die are up to 10 times more likely to die within their first 2 years. Antenatal attendance, access to skilled birth attendants and facility deliveries are low, and quality service delivery is often poor with disparities in access and availability to appropriate assessment and intervention, with delays in delivery, escalation of care and emergency maternity care.

Participants

Inclusion criteria

- Pregnant women aged under 18 at recruitment

Exclusion criteria

- There will be no exclusion criteria in terms of gestational age, as from an ethical and logistical standpoint, all young pregnant women should have access to the intervention, and pregnancy outcome data to be collected at an individual level.

Clusters and participant selection and enrolment

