# Proposed analysis

We will undertake two statistical analyses: one pragmatic, intention to treat analysis (ITT) to compare intervention and control clusters that include all adolescent girls as originally allocated after randomization; and a complementary per protocol (PP) analysis to compare intervention and control clusters that includes only those girls who completed the intervention originally allocated. The CONSORT guidelines for reporting of parallel group RCTs recommend that both ITT and PP analyses should be reported for all planned outcomes to allow readers to interpret the effect of an intervention. It is not possible to blind clusters to interventions they receive, but outcome assessments will be blinded.

The main analysis will be pragmatic and by logistic regression adjusting the standard errors for clustering. This gives equal weight to each woman. A secondary analysis using random effects generalised least squares (GLS-RE) will also be attempted, although past experience is that the model might not converge to give any useable results. We will adjust for important baseline differences that might be related to outcomes (e.g. parity, gestation at first antenatal visits). As individual-specific data will be used there is a potential for missing data; but the main impact of missing data would be to invalidate the randomised comparison if there was unequal dropout between the two arms, leading to potential boas. Multiple regression, as described, would correct for any such bias.

Qualitative data from interviews with women and focus groups discussions with mentors, healthcare providers and stakeholders with be analysed using Braun and Clarke's six-phase approach to thematic analysis^18^. In brief, this includes familiarisation with the data, generation of initial codes, the searching for and review of themes, naming and offering explanations for each theme, and lastly producing a report. This practical analytic approach involves inductive coding practices which are both consultative and initially open^19^, and thus helpful to explore the perspectives of different research participants, highlighting similarities and differences, and generating unanticipated insights^18^.

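### The intention-to-treat set is described as all adolescent girls, but girls enter the data only through facility contact, which the intervention is designed to increase

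*Protocol*

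**What the plan says.** **Target population.** The only inclusion criterion is "Pregnant women aged under 18 at recruitment", with no condition on facility contact. Proposed analysis promises to "include all adolescent girls as originally allocated after randomization".

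**How girls enter the data.** Under Data collection, data collectors visiting the PHUs use the routine registers to "identify under-18-year- presenting at the health facility", whether at antenatal registration, at delivery in the PHU or a referral hospital, or at the 6-week visit. Every row of the scenario table begins with a girl who attends antenatal care, arrives in labour or gives birth at the PHU. The section closes with the assurance that "it is unlikely that most primary outcome events will be missed".

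**Who may be missed.** The Background says that lack of adult support often "leads to delays in care-seeking or complete lack of antenatal and delivery care, putting teenagers at high risk of death". The setting description adds: "Antenatal attendance, access to skilled birth attendants and facility deliveries are low".

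**What the intervention does.** The theory of change states: "Mentors ensure that girls access antenatal care". The intervention description has the mentor go with the girl to register. In intervention sites, girls also come forward themselves or through friends and family after community engagement; no control equivalent is described.

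**Death detection.** For girls who attended antenatal care but did not deliver at the PHU, the last tracing step is a link to MDSR midwife investigators. It is specified for intervention sites only.

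**The concern.** In a cluster trial, an intention-to-treat comparison needs participants to be identified in a way that allocation does not affect. Here identification follows randomisation and runs through facility contact, which mentoring is meant to change. A girl who would have had no contact under usual care is likely to be registered in an intervention cluster and unseen in a control cluster. If such girls are at above-average risk, as the Background indicates, the intervention arm takes in extra high-risk pregnancies and the control arm does not. Restricting the MDSR link to intervention sites pushes the same way. This is identification bias.

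Proposed analysis says that multiple regression would correct the bias from unequal dropout. That cannot extend to this problem, because a girl with no record contributes neither covariates nor an outcome. The pilot's feasibility questions include recruitment, data collection and the choice of primary outcome, so an unrecognised arm-dependent denominator could pass into the definitive trial.

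**Working it through.** **Which girls are unseen.** Checked against the entry routes and the scenario table:

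- Attends antenatal care: enters in both arms.
- No antenatal care, but arrives at the PHU in labour, delivers at the referral hospital or attends at 6 weeks: enters in both arms.
- No contact at any of these points: no row and no entry route in control clusters. In intervention clusters, community enrolment followed by accompanied registration is a route.

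The unseen group is therefore girls with no facility contact at all, which is narrower than girls without antenatal care.

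**Inputs.** The protocol gives no figure for this group, so there is none to reproduce. Two figures in Sample size calculation bear on it: the planning risk of 20%, and the finding that at least 16% of teenage deliveries at one typical PHU had an event. The 16% is itself a facility rate, and it leaves out late neonatal deaths and emergency referrals. The following are assumptions: no-contact share q = 10-30%, risk in that group r = 30% or 40%, and the fraction f of them that mentoring brings into the registers = 0.5 or 1.

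**Formulas, with no true effect and a true risk of 20% in both arms.**

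- Observed control risk: r0 = (0.20 - q·r)/(1 - q)
- Observed intervention risk: r1 = [(1 - q)·r0 + f·q·r]/(1 - q + f·q)
- Spurious risk ratio: r1/r0

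Example with q = 0.2 and r = 0.3: r0 = (0.20 - 0.06)/0.8 = 17.5%. With f = 0.5, r1 = (0.14 + 0.03)/0.9 = 18.9%, ratio 1.08. With f = 1, r1 = 20%, ratio 1.14.

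| q | r | Observed control risk | At least 16%? | Ratio, f = 0.5 | Ratio, f = 1 |
| --- | --- | --- | --- | --- | --- |
| 10% | 30% | 18.9% | yes | 1.03 | 1.06 |
| 10% | 40% | 17.8% | yes | 1.07 | 1.13 |
| 20% | 30% | 17.5% | yes | 1.08 | 1.14 |
| 20% | 40% | 15.0% | no | 1.19 | 1.33 |
| 30% | 30% | 15.7% | no | 1.16 | 1.27 |
| 30% | 40% | 11.4% | no | 1.44 | 1.75 |

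The three rows consistent with the 16% give ratios of 1.03 to 1.14. With a true risk of 20%, no combination that respects the 16% can exceed 0.20/0.16 = 1.25.

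**With a real effect.** Suppose mentoring multiplies every girl's risk by 0.45 (20% to 9%) and f = 1. The observed ratio is then 0.45 times the tabulated one: 0.45 × 1.06 = 0.48 to 0.45 × 1.14 = 0.51 over the same three rows.

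**Can counts alone reveal it?** Over those rows the intervention denominator grows by a factor (1 - q + f·q)/(1 - q), from 0.95/0.90 = 1.06 to 1/0.80 = 1.25. The twelve site counts in Appendix 1 (births under 19) run from 28 to 65, with mean 42 and SD about 12.3. The difference between two six-site totals then has SD √12 × 12.3 ≈ 43, about 17% of the expected 252 per arm, ignoring matching. A raw between-arm difference is therefore a weak signal.

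**The case against.** Several points on the other side stand.

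- **The unseen group is narrow and unmeasured.** A reader might infer from the remarks on low attendance that every control girl without antenatal care is lost. The entry routes do not support that, since labour, referral-hospital and 6-week contacts count in both arms.
- **Large distortions conflict with the protocol's own rate.** A reader might take a spurious ratio as high as 1.75 from the full grid. That needs an observed control risk of 11.4%, below the 16% already found in PHU records. The limit on this point is that the 16% comes from one PHU, and a true risk above 20% would readmit some excluded rows. For example, at an assumed 25% with q = 20%, r = 40% and f = 1, control risk is (0.25 - 0.08)/0.8 = 21.25% and the ratio is 1.18.
- **The control rate is not shown to be wrong for planning.** It is tempting to say that the rate carried into the definitive sample size is too low. If that trial uses the same registers, the register-based rate is the relevant input.
- **The protocol has partial safeguards.** Reach compares participants with the site population, data completeness is a primary feasibility outcome, and a community survey is allowed. However, Reach recovers no control outcomes. The survey is optional, limited to low-count clusters and aimed at numbers and age reporting. Hospital cross-checks and address visits need an earlier record, and CHW tracing is tabled for girls who delivered at the PHU.
- **The aim is feasibility.** The effect estimate is not the main deliverable. This lowers the urgency, but how girls are identified is itself a feasibility question.

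**Conclusion.** The point holds as a contradiction between the stated intention-to-treat population and the way girls are identified, with an arm-dependent mechanism built into the intervention. The bias in the composite most likely runs against 2YL, provided that girls without facility contact are at higher risk than the rest. The documents do not fix its size. The 1.03 to 1.14 range illustrates what is compatible with a true risk of 20% and an observed control risk of at least 16%; it is not an estimate. It would be larger if the true risk exceeds 20% or the no-contact share is higher. The documents do not support a claim that the trial will show spurious harm, or that all control events outside antenatal care go unrecorded.

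**What to change.** 1. In Proposed analysis, restate the analysed set as under-18 girls identified through a participating PHU or its referral hospital, and state that identification can differ by arm. Withdraw the claim that regression corrects the bias, and withdraw the unqualified assurance on missed events in Data collection. The new wording makes the claim accurate but does not remove the bias, so the remaining steps are needed.
2. In the scenario table, state that the MDSR link and all other tracing steps apply identically in intervention and control sites.
3. Report, as a feasibility result, the number of girls identified per cluster by arm and the route and timing of first identification. Set these against a pre-allocation register count of under-18s. Appendix 1 counts 2020 births under 19, so the under-18 count has to be extracted from the registers. Note that between-arm count differences are noisy with six sites per arm.
4. Add a bounding analysis, labelled as assumption-based, over stated ranges for the no-contact share, the risk in that group and the fraction brought in.
5. If the community survey is run, choose clusters by the same rule in both arms.

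The cost is a narrower stated population, a less favourable statement on completeness, and modest extra register and analysis work.

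### Finding of primary-outcome events may be adapted site by site without a minimum standard, and one tracing step is written for intervention sites only, so detection of deaths can differ by cluster and by arm

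*Protocol*

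**What the plan says.** All of this is in the protocol, mainly under Data collection.

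- **Common sources and steps.** Four routine records are listed for use at PHUs: the antenatal, birth and referral registers and the 6-week appointment book. A scenario table adds a referral-hospital cross-check, a visit to the registered address, liaison with the referral co-ordinator, and community health worker (CHW) follow-up: "CHWs are routinely sent out to check on women who default at 6 weeks". On who does the work: "Data collection at intervention and control sites will be done by data collectors".
- **Permission to vary.** Straight after the assurance that "it is unlikely that most primary outcome events will be missed" comes the sentence "We will apply a flexible approach to individualise our methodology according to local capacity and CHW workforce infrastructure".
- **A step written for one arm.** For a girl who attended antenatal care but did not give birth at the PHU, the last step is: "Connection with midwife investigators from MDSR teams in intervention sites to detect any maternal deaths in community".
- **A source held by some sites.** "At some PHUs, an additional ‘adolescent book’ is in use to record ANC registration of under-18-year-olds and associated birth outcomes".
- **Checks.** The research assistant will "validate 10% of the source data to check for transcription errors". Proposed analysis states that outcome assessments are blinded, without saying how.
- **Balance.** Under Randomisation, the minimisation factors are PHU use and distance to the referral hospital. Registers and CHW capacity are not among them.

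**The concern.** The composite of maternal death, stillbirth and neonatal death is counted only when someone finds the event. If the search differs between clusters, the observed risk in a cluster mixes true risk with local detection. With 6 clusters per arm, such differences need not average out, and a step used in one arm only does not average out at all.

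Three things are at stake:
- the direction and size of the observed contrast;
- the event rate and intra-cluster correlation (ICC) to be carried into the definitive trial, since sample size calculation is one of the primary feasibility outcomes;
- the data-completeness feasibility outcome, which cannot be read cleanly if each site may define its own search.

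The assurance offered is weak, because missing a substantial minority of events is compatible with not missing most of them.

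**Working it through.** **1. The plan's own figure.** Sample size calculation gives 42 deliveries per site, 20% v 9%, ICC 0.02 and 84% power. Two-sided 5% is assumed here because alpha is not stated.
- Design effect = 1 + 41 × 0.02 = 1.82. Six clusters per arm give 252 / 1.82 = 138.5 effective girls per arm.
- SE = √[1.82 × (0.20×0.80 + 0.09×0.91) / 252] = 0.0418.
- Power = Φ(0.11/0.0418 − 1.96) = Φ(0.67) = 75% (74% with a pooled variance).

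The stated 84% is not reproduced with 12 clusters. Sixteen, the number still given under Randomisation, yield 85%. That is a separate matter; 75% (unpooled) or 74% (pooled) is the baseline below.

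**2. Unequal detection between arms.** Observed risk = true risk × detection, counting untraced girls as event-free. All detection rates are assumptions.
- 95% intervention, 80% control: control 0.20×0.80 = 0.160; intervention 0.09×0.95 = 0.0855; RR = 0.53 instead of 0.45. SE = √[1.82 × (0.160×0.840 + 0.0855×0.9145)/252] = 0.0392; power = Φ(0.0745/0.0392 − 1.96) = 48%.
- Reversed: 0.20×0.95 = 0.190 v 0.09×0.80 = 0.072, RR 0.38. With no true effect, 0.190 v 0.160, RR 0.84.

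Range (power and error rates by the pooled formula):

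| Detection, control / intervention | RR if true RR is 1 | RR if true RR is 0.45 | Consequence |
|---|---|---|---|
| 90% / 90% | 1.00 | 0.45 | power 69% |
| 80% / 90% | 1.12 | 0.51 | power 52% |
| 90% / 80% | 0.89 | 0.40 | false claim of benefit 6.5%, not 2.5% |
| 90% / 70% | 0.78 | 0.35 | false claim of benefit 14.6% |

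**3. Does this depend on the denominator?** Suppose instead that girls with unfound events leave the analysis. At 95% v 80%, control is 0.160/(1 − 0.040) = 0.167 and intervention 0.0855/(1 − 0.0045) = 0.086, so RR = 0.52. Reversed with no effect: 0.160/0.960 = 0.167 against 0.190/0.990 = 0.192, RR 0.87. The direction is the same and the size slightly smaller. If girls are lost independently of outcome and excluded, the risk ratio is not biased.

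**4. Detection varying by cluster but unrelated to arm.** Take mean detection m = 85% with between-cluster SD s. Observed between-cluster variance = (m² + s²) × 0.02 × p(1−p) + p²s². The SD of the chance difference in mean detection between arms is s√(2/6).

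| s | Observed control ICC | Power | SD of arm difference in detection |
|---|---|---|---|
| 0 | 0.016 | 70% | 0 |
| 0.10 | 0.019 | 68% | 0.06 |
| 0.15 | 0.023 | 65% | 0.09 |

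The loss of power is modest. The chance arm difference is the larger issue.

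**5. The extra register.** The number of PHUs with the book is not stated. If 5 of 12, and treating allocation as a simple draw of 6 from 12, a 4–1 or 5–0 split has probability 2 × (90/792 + 6/792) = 24%. If 3 of 12, all three fall in one arm with probability 2 × 20/220 = 18%.

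**6. Timing.** Pre-pilot trial plans to confirm data collection procedures between September 2021 and January 2022. Trial duration places randomisation in March 2022. The version in force is dated 21 July 2023 and itself discloses one community's allocation. The permission to adapt is in the future tense in that version, so it can still be used with allocation known.

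**The case against.** Much of a common procedure is already written: four registers, a tracing table, and data collectors in both arms. This is also a pilot, and learning which tracing works locally is part of its purpose. Both points are fair. But the permission to adapt follows the table and removes its force as a minimum, and an uncontrolled mixture of methods is hard to evaluate even in a pilot.

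The existing checks do not close the gap. The 10% check concerns transcription, not unfound deaths. Missing-data alerts cannot flag a girl who was never registered. CHW follow-up depends on the workforce by which methods may vary. Confirming procedures before randomisation does not bind sites when the current text still allows adaptation.

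A reader might infer more than the document supports:
- *That detection was set after allocation by staff who knew the arm.* The text shows only that adaptations can still be made then. It states that outcome assessment is blinded, although no mechanism is described.
- *That the adolescent book is a source of post-allocation bias.* It was already in use, so randomisation balances it in expectation. It brings chance imbalance and between-cluster variance.
- *That mentors and coordinators raise detection in intervention sites.* Nothing in the protocol makes them a source of outcome notification.
- *That the MDSR step could produce a gap as wide as 95% v 80%.* It concerns only maternal deaths, and only girls who did not give birth at the PHU. The reference to intervention sites may also be loose wording.

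**Conclusion.** The point holds in limited form. As written, one tracing step differs by arm, other steps may be varied by site without a stated floor, and one source exists at an unstated subset of PHUs outside the minimisation. Detection can therefore differ by cluster and by arm, and nothing in the protocol prevents it. It does not follow that detection does differ, or in which direction. Taken literally, the MDSR wording would favour detection in the intervention arm and so hide benefit; site adaptations could act either way.

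The sizes are hypothetical. A gap of 10 to 20 percentage points in detection moves a null risk ratio to between 0.78 and 1.12 in the cases tabulated. This assumes 6 clusters of 42 per arm, ICC 0.02, and untraced girls counted as event-free. Shared under-detection leaves the risk ratio unchanged and costs only power.

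**What to change.** Replace the sentence on a flexible approach with one minimum case-finding and tracing sequence for all 12 clusters in both arms:

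- the four routine registers, the referral-hospital cross-check, the address visit and CHW follow-up;
- the MDSR link in both arms or in neither;
- a fixed number of contact attempts and a deadline after birth.

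Allow local additions, including the existing adolescent book, only as logged extras by cluster. Do not issue new books now: that would change detection partway through and could not repair data already collected.

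Count every event, whatever its source, and record the source of first notification. Run a sensitivity analysis limited to events found by the common sequence. Report by arm the proportion of registered girls with confirmed 42-day maternal status and 28-day infant status. The analysis detail may sit in the SAP, but the source field must be collected under the protocol.

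The cost is a wording change, one data field, a deviation log and slightly less freedom for local teams.
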